### Interventions

Patients were administered with >6 mg dexamethasone or an equivalent corticosteroid for a minimum of 3 consecutive days (Table 1). Our study permits the use of other general concurrent interventions, such as venous thromboembolism prophylaxis, fever and glucose control, fluid management, antibiotics, and antiviral drugs. The use of other immunomodulatory agents such as baricitinib, JAK inhibitors, and interleukin 6 pathway inhibitors, as well as antiviral drugs such as remdesivir, is allowed as part of a clinical trial or hospital policy. However, a sensitivity analysis will be performed excluding these patients.

### Outcomes

#### Primary Outcomes

Several outcome parameters will be studied for the different work packages based on the available data. In WP1A, the primary outcome of interest is hospital mortality in patients who do not receive high-flow nasal canule or invasive mechanical ventilation due to restrictions in care, either on medical grounds or advance directives of the patient. In patients who do not have restrictions in care, the need for high-flow nasal canule or invasive mechanical ventilation will be the primary outcome of interest (WHO severity 6-9). In WP1B, WP2, and WP3, 28-day survival and 28-day need for invasive mechanical ventilation will be studied as primary outcomes. In WP4, we will study the response to corticosteroids using the same outcomes.

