### Patient Selection and Inclusion Criteria

Adult patients (≥18 years) hospitalized with polymerase chain reaction–confirmed COVID-19 or high clinical suspicion of COVID-19 will be included (Figure 3). Pregnant patients and patients receiving corticosteroids for other conditions during or prior to hospital admission are eligible, although a prespecified sensitivity analysis excluding these patients will be performed. Patients who die within 48 hours after admission or patients who object to participate will be excluded from the study. In WP1 and WP4, we will include patients from all SARS-CoV-2 epidemic waves, and in WP2-3, we will include patients from the first and second waves only. Specific inclusion and exclusion criteria for each work package will be applied. In WP1A, patients will be included who are admitted to the ward with a World Health Organization clinical progression scale class of 4-5 [19] (ie, no oxygen or oxygen therapy via a cannula or [non-rebreather] mask). WP1B includes patients who have progressed to the World Health Organization clinical progression scale class of 5-6 (ie, noninvasive oxygen therapy, including conventional oxygen via cannula [non-rebreather] mask, high-flow nasal cannula, noninvasive continuous positive airway pressure, and noninvasive bilevel positive airway pressure) after in-hospital treatment with 10 days of 6 mg per day dexamethasone. The study population for WP2-4 consists of patients admitted to the ICU for a period exceeding 48 hours, who received invasive mechanical ventilation via an endotracheal tube, a tracheostomy, or extracorporeal membrane oxygenation during their ICU stay.

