**Figure 3 figure3:**
[figure not shown]
Patient inclusion. World Health Organization (WHO) classification: 0=uninfected, 1=asymptomatic; viral RNA detected, 2=symptomatic; independent, 3=symptomatic; assistance needed, 4=hospitalized; oxygen by mask or nasal prongs, 5=hospitalized; oxygen by mask or nasal prongs, 6=hospitalized; oxygen by noninvasive ventilation or high flow, 7=intubation and mechanical ventilation partial pressure of oxygen in arterial blood–fraction of inspiratory oxygen concentration (PaO2/FiO2) ratio of ≥150, 8=mechanical ventilation PaO2/FiO2 ratio of <150 or vasopressors, 9=mechanical ventilation PaO2/FiO2 ratio of <150 and vasopressors, dialysis or extracorporeal membrane oxygenation, 10=dead. PCR: polymerase chain reaction; WP: work package.

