In WP1, WP2, and WP3, several statistical analysis approaches will be considered to determine the association between high-dose corticosteroids and outcome, and statistical analyses will depend on the structure of the available data. A multivariable logistic regression model will be used with high-dose corticosteroids as exposure and survival at day 28 as an outcome. Covariates used for adjustment will include age, gender, BMI, smoking status, prior administration of corticosteroids during admission, comorbidity, sequential organ failure assessment score, oxygen saturation, partial pressure of oxygen in arterial blood–fraction of inspiratory oxygen concentration ratio, C-reactive protein, procalcitonin, ferritin, interleukin 6, D-dimer, lactate dehydrogenase, platelet count, lymphopenia, and level of respiratory support. Covariates can be added or removed based on insights from the data set or from the literature. A model might be constructed in which patients are matched on a propensity score based on their probability to receive high-dose corticosteroid treatment. Propensity scores will be determined using a logistic regression model with high-dose corticosteroids as a dependent variable and determinants of high-dose corticosteroids as independent variables. After matching, survival and mortality at day 28 and other outcome parameters will be compared between matched groups using logistic regression. A Cox proportional hazards model might be performed to determine the effect of high-dose corticosteroids on time to death while taking into account the days of administration using time-dependent covariates. Other approaches involving censoring weights for differential loss to follow-up (eg, marginal structural models) or competing risks (eg, joint models) might be explored.

Furthermore, we will use clinical and biological data to perform latent class analysis to search for subphenotypes, which respond more favorably to corticosteroid treatment. This heterogeneity of treatment effect will be evaluated by including the latent class analysis-derived subphenotype, corticosteroid exposure, and an interaction term of the 2 as c-variate in the above-described survival models. Heterogeneity of treatment effect is considered to be present if the interaction term has a *P* value of <.05.

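### WP1A primary outcome: death is left out of the event for unrestricted patients, and the mortality stratum is defined by care not received after admission, so the strata are post-baseline and not exhaustive

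*Protocol article*

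**What the plan says.** The Primary Outcomes section gives WP1A two primary outcomes, one per stratum.

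- Restricted patients: "hospital mortality in patients who do not receive high-flow nasal canule or invasive mechanical ventilation due to restrictions in care", where the restriction is "either on medical grounds or advance directives of the patient". No time is given by which it must be in place.
- Those with no restriction: "the need for high-flow nasal canule or invasive mechanical ventilation will be the primary outcome of interest (WHO severity 6-9").

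The Figure 3 caption gives the scale, which ends: "9=mechanical ventilation PaO2/FiO2 ratio of <150 and vasopressors, dialysis or extracorporeal membrane oxygenation, 10=dead".

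Patient Selection and Inclusion Criteria removes only early deaths: "Patients who die within 48 hours after admission or patients who object to participate will be excluded from the study".

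For WP1, WP2 and WP3 together, Statistical Analysis states: "A multivariable logistic regression model will be used with high-dose corticosteroids as exposure and survival at day 28 as an outcome". Competing-risk methods are listed there only as an option that might be explored. Secondary Outcomes lists in-hospital mortality for the ICU work packages, not for WP1A.

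**The concern.** Three features of the definition matter.

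1. **Death lies outside the event.** With a yes/no outcome covering classes 6 to 9, a ward death without escalation is coded like a recovery.
2. **Stratum membership depends on later care.** Not receiving escalation because of a restriction can be known only after the patient has deteriorated. WP1A studies initial treatment, which is meant to change that course. A restriction set on deterioration would move a patient from one endpoint to the other.
3. **The two strata are not complements.** Being denied escalation because of a restriction and having no restriction leave other patients in between.

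At stake is whether the WP1A comparison means the same thing in both exposure groups. Data Collection contrasts high-dose with low-dose centers, and Study Design and Setting also uses differences between epidemic waves. Escalation and restriction practice could differ along those same lines. Restriction status is not among the covariates named in Statistical Analysis, although that section allows covariates to be added.

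**Working it through.** The article states no event rate, effect size or sample size for WP1A, so there is no figure to reproduce. The check is a reading of the definition, followed by arithmetic on assumed rates.

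**Step 1. Patient types under the literal text**

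| WP1A patient | Primary outcome |
|---|---|
| No restriction, receives high-flow or ventilation | Event (class 6-9) |
| No restriction, dies after 48 hours without either | Non-event (class 10 is outside 6-9) |
| Restricted, needed escalation, not given it | Hospital mortality |
| Restricted, never needed escalation | Neither stratum |
| No-intubation directive, receives high-flow | Unclear: neither stratum if *or* means that neither therapy was given; mortality if it means that one of the two was withheld |
| No restriction at admission, restricted on deterioration, not escalated | Moves to the mortality stratum |

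**Step 2. Deaths without escalation (assumed rates)**

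Let the risk of escalation or death (6-10) be 30% in both groups, so there is no true difference. The 6-9 risk is 30% minus the risk of direct death.

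| Direct death, low vs high dose | 6-9 outcome, low vs high dose | Odds ratio |
|---|---|---|
| 1% vs 1% | 29% vs 29% | 1.00 |
| 1% vs 2% | 29% vs 28% | 0.95 |
| 1% vs 3% | 29% vs 27% | 0.91 |
| 2% vs 5% | 28% vs 25% | (0.25/0.75)/(0.28/0.72) = 0.86 |
| 3% vs 1% | 27% vs 29% | 1.10 |

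**Step 3. Restriction set on deterioration (assumed rates)**

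Let p be the share who deteriorate and r the share of those who are then restricted. The event risk left in the unrestricted stratum is p(1-r)/(1-pr).

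- p = 30% in both groups, r = 20% in both: 25.5% vs 25.5%. No bias.
- p = 30% in both, r = 20% (low) vs 40% (high): 0.24/0.94 = 25.5% vs 0.18/0.88 = 20.5%. The difference is -5.1 points; the true one is 0.
- p = 30% vs 24%, r = 30% in both: 0.21/0.91 = 23.1% vs 0.168/0.928 = 18.1%. The difference is -5.0 points; the true one is -6.
- p = 30% vs 24%, r = 40% vs 20%: 0.18/0.88 = 20.5% vs 0.192/0.952 = 20.2%. The difference is -0.3 points; the true one is -6.

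**Step 4. Literal mortality stratum (assumed rates)**

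Among restricted patients, let the high dose halve the need for escalation from 40% to 20%. Let mortality be 70% if escalation was needed and 5% otherwise.

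- Only those denied escalation: 70% vs 70%.
- All restricted patients: 0.4×0.70 + 0.6×0.05 = 31% vs 0.2×0.70 + 0.8×0.05 = 18%.

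The literal stratum drops the patients in whom treatment prevented deterioration.

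**The case against.** The two-stratum design looks like a deliberate answer to competing death: where escalation is withheld, mortality is the endpoint. Unrestricted patients can by definition be escalated, so most who deteriorate would count as events before dying, and deaths within 48 hours are already excluded. The remaining direct deaths are probably few. Advance directives often predate treatment, and the phrase about not receiving escalation may be loose wording for not being eligible for it. All of this limits the likely size, but it does not repair the text. No other section of the article restores the omitted deaths to the WP1A primary outcome or dates the restriction.

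A reader might infer more than the article supports:

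- **That the protocol treats death as a good outcome.** It does not say so. The non-event coding follows from the 6-9 range.
- **That a sizeable share of miscoded events is a bias of that size.** With assumed escalation of 15-20% and direct death of 1-3%, the omitted share is 0.01/0.21 = 4.8% to 0.03/0.18 = 16.7%. This is misclassification, and equal direct-death rates produce no false difference.
- **That partly restricted patients have no outcome.** For a no-intubation patient on high-flow this depends on how *or* is read. Day-28 survival would still be available in any case.
- **That the wrong outcome is modelled.** The day-28 sentence covers WP1 to WP3 together and matches a stated primary outcome of WP1B, WP2 and WP3. The paragraph presents its approaches as dependent on data structure and adds other outcome parameters after matching. The sentence does not name the WP1A outcomes, but it does not replace them.

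A single composite for everyone is also partly a matter of preference. In fully restricted patients, death is the only route to an event, so separate endpoints are defensible if the strata are clear.

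**Conclusion.** The point holds in a limited form. Two defects follow from the text without any assumed rate: class 10 lies outside the unrestricted event, and the mortality stratum is defined by post-admission care that excludes restricted patients who never needed escalation. The place of no-intubation patients who receive high-flow is ambiguous. That restrictions are set after treatment start is left open by the article, not stated.

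The size cannot be determined from the article. Where treatment has no effect, a false difference needs direct deaths or restriction practice to differ between exposure groups. Under the assumed rates, the first gives odds ratios of 0.86 to 1.10 and the second an apparent 5.1-point benefit. Where treatment does have an effect, unequal restriction practice can shrink a 6-point difference to 0.3, and the literal mortality stratum can hide an effect even when practice is the same in both groups. These figures show direction and possibility; they are not estimates for this study. The definition should be corrected before the WP1A analysis.

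**What to change.** - Classify restriction status at or before treatment start, in categories that cover everyone: none, no invasive ventilation, and neither high-flow nor invasive ventilation. State the outcome that applies to each.
- In unrestricted patients, count escalation or death (WHO 6-10) within a fixed window such as 28 days.
- In all patients restricted at baseline, use mortality, whether or not escalation was later needed. The alternative is the 6-10 composite for everyone, with baseline restriction as covariate and subgroup.
- Report escalation and death separately beside any composite.
- Name these outcomes for WP1A in Statistical Analysis, alongside day-28 survival.

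The cost is mainly wording and recoding. Data collection was still open when the article was written (1500 patients by April 2023, completion expected by December 2023). The one real condition is that restriction status at admission can be retrieved from the records. The article does not say that it is collected, so this should be checked first.

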### Study Aims

#### Work Package 1: High-Dose Corticosteroid Treatment in the Ward

Work package 1A (WP1A) is used to investigate whether initial treatment with high-dose corticosteroids compared to treatment with 6 mg dexamethasone per day for 10 days, or an equivalent corticosteroid, improves patient outcomes in the ward (Figure 1).

WP1B is used to investigate whether treatment with high-dose corticosteroids compared to no corticosteroids, after treatment with 6 mg dexamethasone per day for 10 days, improves patient outcomes in the ward.

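### WP1B takes 28-day need for invasive ventilation as a primary outcome without the care-restriction split used in WP1A, so patients barred from ventilation cannot have the event

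*Protocol article*

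**What the plan says.** All references are to the protocol article.

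- **Primary Outcomes, WP1A.** The outcome depends on restriction status. For restricted patients it is "hospital mortality in patients who do not receive high-flow nasal canule or invasive mechanical ventilation due to restrictions in care". For the others: "In patients who do not have restrictions in care, the need for high-flow nasal canule or invasive mechanical ventilation will be the primary outcome", which the article ties to WHO severity 6-9.
- **Primary Outcomes, WP1B.** The rule is shared with the two ICU work packages and has no split: "In WP1B, WP2, and WP3, 28-day survival and 28-day need for invasive mechanical ventilation will be studied as primary outcomes".
- **Study Aims, Work Package 1.** WP1B is a ward question, as WP1A is. It asks whether high-dose treatment, "after treatment with 6 mg dexamethasone per day for 10 days, improves patient outcomes in the ward".
- **Patient Selection and Inclusion Criteria.** "WP1B includes patients who have progressed to the World Health Organization clinical progression scale class of 5-6", after the 10-day course. The general exclusions are: "Patients who die within 48 hours after admission or patients who object to participate will be excluded from the study". Restriction in care appears in neither place. The section also says "Specific inclusion and exclusion criteria for each work package will be applied", but those written out for WP1B do not mention restriction.
- **Statistical Analysis.** The adjustment list covers demographics, comorbidity, organ failure score, oxygenation, laboratory values and level of respiratory support. Restriction in care is not on it. The list may be altered, and competing-risk methods are optional.

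**The concern.** The article recognises for WP1A that an escalation outcome is not meaningful in a patient who will not be escalated. The same reasoning applies to WP1B, which follows ward patients later in their stay, but there the outcome is named without the limit.

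Take three WP1B patients: one with a restriction against IMV who worsens and dies unventilated, one without a restriction who worsens equally and is intubated, and one who recovers. If need is read as receipt, the first and third share the value no IMV, and only the second has the event. On this outcome the death counts as a good result.

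What is at stake is the WP1B comparison on one of its two primary outcomes. If restriction is more common in one exposure group, the IMV comparison partly measures that difference and not the effect of corticosteroids. The issue falls mainly on WP1B, because WP2 and WP3 enrol patients who received IMV.

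**Working it through.** **Step 1: does the text deal with restriction anywhere in WP1B?**

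| Place | WP1A | WP1B |
|---|---|---|
| Setting | Ward | Ward |
| Escalation outcome | Patients without restrictions only | No limit stated |
| Outcome for restricted patients | Hospital mortality | Nothing separate stated |
| Eligibility or exclusion on restriction | None needed, because the outcome is split | None written |
| Restriction among listed covariates | No | No |

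It does not.

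**Step 2: how would need be scored?** The article does not say. The data are routinely collected and retrospective, and need in WP1A is tied to a WHO class range that records support given. Receipt of IMV is therefore the practical reading, and a patient barred from IMV has event probability zero.

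**Step 3: size.** The article gives no IMV rate, restricted share or WP1B group size, so there is no figure to reproduce. All rates below are assumptions.

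Let p be the IMV risk in unrestricted patients and r the restricted share of a group. Then:

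- observed IMV risk = p × (1 − r)
- odds ratio (OR) = [p₁/(1 − p₁)] / [p₀/(1 − p₀)], using observed risks, high-dose over comparator

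*Unequal restriction, no true effect (p = 0.30 in both groups)*

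| Restricted, high-dose vs comparator | Observed IMV risk | OR |
|---|---|---|
| 20% vs 20% | 24% vs 24% | 1.00 |
| 30% vs 20% | 21% vs 24% | 0.84 |
| 40% vs 20% | 18% vs 24% | 0.70 |
| 20% vs 40% | 24% vs 18% | 1.44 |

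For the third row: 0.30 × 0.60 = 0.18 and 0.30 × 0.80 = 0.24, so OR = (0.18/0.82)/(0.24/0.76) = 0.2195/0.3158 = 0.70. In unrestricted patients alone the OR is 1.00 in every row.

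*Equal restriction, true effect (p = 0.30 in the comparator, 0.20 on high-dose)*

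| Restricted share, both groups | Observed IMV risk, high-dose vs comparator | Risk difference | OR | n per group, 80% power, two-sided 5% |
|---|---|---|---|---|
| 0% (unrestricted only) | 20% vs 30% | −10 points | 0.58 | 294 |
| 20% | 16% vs 24% | −8 points | 0.60 | 392 |
| 40% | 12% vs 18% | −6 points | 0.62 | 555 |

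The risk difference shrinks by the factor 1 − r. The risk ratio stays at 0.20/0.30 = 0.12/0.18 = 0.67, and the OR moves only from 0.58 to 0.62.

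The 294 counts analysed unrestricted patients. With 40% restricted, reaching it takes 294/0.60 = 490 ward patients per group, against 555 when everyone is counted. The loss of precision is real but modest.

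**The case against.** The strongest reply is that the article never says restricted WP1B patients enter the IMV analysis as non-events. A reader might infer such a scoring rule, but none is written. One sentence names two outcomes for three work packages, further criteria are announced, the patient inclusion figure is not shown, and a fuller protocol or analysis plan may define the analysis set. This stands as a limit on wording. It does not remove the point, because the article itself states a split for one ward work package and an outcome without it for the other.

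Other replies, and what stands of each:

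- **Deaths are not lost.** Correct: 28-day survival is also primary in WP1B and separates the patient who dies from the one who recovers. It would be wrong to infer that WP1B ignores these deaths. But IMV is a primary outcome in its own right, and survival does not correct its estimate.
- **Adjustment may absorb the imbalance.** Age, comorbidity, organ failure score and respiratory support may correlate with restriction, determinants of high-dose use are to be studied first, and covariates may be added. The crude odds ratios above are therefore not the expected error of the planned analysis. These provisions permit a correction without committing to one.
- **The imbalance is assumed.** Correct. The documents give no evidence that restriction differs between exposure groups, or in which direction. A reader might infer that the IMV result will favour high-dose treatment; nothing supports that.
- **Dilution is overstated.** A reader might take the fall from 10 to 6 points as a serious weakening of the effect. The article plans logistic regression, and on the odds ratio scale balanced restriction changes little.

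**Conclusion.** The point holds as an inconsistency between the two ward work packages: WP1A limits the escalation outcome to patients without restrictions in care, and WP1B uses 28-day need for IMV with no such limit and no other stated provision for restriction. It rests on reading need as receipt, which retrospective routine data in practice require.

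The consequence depends on balance. With unequal restriction the IMV odds ratio is biased in a direction that cannot be known beforehand: 0.70 or 1.44 for a 20-point imbalance either way and 0.84 for 30% against 20%, all crude, with no true effect and an assumed 30% IMV risk. With equal restriction the odds ratio is nearly intact, and the cost is a smaller absolute difference and lower precision. The defect is confined to the IMV outcome in WP1B and should be corrected before analysis.

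**What to change.** Extend the article's own WP1A logic to WP1B:

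1. Analyse 28-day IMV only in patients with no restriction against IMV recorded by WP1B time zero, the end of the 10-day course.
2. Use 28-day survival as the primary outcome for patients with such a restriction.
3. Fix restriction status at time zero, not by what was later received or withheld.
4. Add restriction status at time zero as a covariate in the WP1B 28-day survival model.

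Entering restriction as a covariate in an all-patient IMV model is not a good substitute, because the restricted stratum would have no events. A composite of IMV or death, or death without IMV as a competing event, could also be defended, but each answers a somewhat different question.

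**Cost.** Fewer patients enter the WP1B IMV analysis, though those removed could not have had the event. It would be too optimistic to call this a change of wording only. WP1A already needs restriction status, but the article does not say that it is collected with a date. Dating it to WP1B time zero may take some extra record extraction across the 22 hospitals.

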#### Work Package 2: High-Dose Corticosteroid Treatment in the ICU

Work package 2 (WP2) is used to investigate whether initial treatment with high-dose corticosteroids compared to treatment with 6 mg dexamethasone per day for 10 days, or an equivalent corticosteroid, improves patient outcomes in the ICU.

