#### Work Package 3: High-Dose Corticosteroid Treatment After Standard Corticosteroid Treatment in the ICU

Work package 3 (WP3) is used to investigate whether treatment with high-dose corticosteroids compared to no corticosteroids, after treatment with 6 mg dexamethasone per day for 10 days, improves patient outcomes in the ICU.

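### In WP2 the primary outcome of 28-day need for invasive ventilation is guaranteed by the entry criteria; WP3 leaves it undefined, and WP4 may inherit it

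*Protocol article*

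**What the plan says.** **Population.** Under Patient Selection and Inclusion Criteria: "The study population for WP2-4 consists of patients admitted to the ICU for a period exceeding 48 hours, who received invasive mechanical ventilation". The sentence goes on to list the routes and ends with "extracorporeal membrane oxygenation during their ICU stay". The criterion is therefore IMV at any time in the stay. It is not tied to the start of corticosteroids or to any other time zero.

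**Primary outcomes.** Under Primary Outcomes: "In WP1B, WP2, and WP3, 28-day survival and 28-day need for invasive mechanical ventilation will be studied as primary outcomes". For WP4: "In WP4, we will study the response to corticosteroids using the same outcomes".

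**Contrast with WP1B.** "WP1B includes patients who have progressed to the World Health Organization clinical progression scale class of 5-6", that is, patients on non-invasive support at entry.

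**Treatment questions.** WP2 compares "initial treatment with high-dose corticosteroids compared to treatment with 6 mg dexamethasone per day for 10 days" (or an equivalent corticosteroid). WP3 compares high-dose corticosteroids with none "after treatment with 6 mg dexamethasone per day for 10 days, improves patient outcomes in the ICU".

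**Secondary outcomes.** For the ICU work packages these already include duration of mechanical ventilation and ventilator-free days.

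**The concern.** A primary outcome has to be able to differ between the groups. Where receipt of IMV is both an entry condition and the event counted, it cannot. WP2 would then have one usable primary outcome rather than two, and a null result on ventilation would be an artefact of selection.

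The second issue is timing. WP2 asks about initial treatment in the ICU, but membership of the cohort is settled by what happens later in the stay. A patient who starts corticosteroids in the ICU, is never intubated and recovers is not in the analysis. If treatment affects the chance of intubation, the two groups are filtered differently, and 28-day survival is compared in what remains. Covariate adjustment or propensity matching among included patients cannot bring the excluded ones back.

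**Working it through.** The article states no event rate, sample size or power, so there is no figure to reproduce. The check sets the entry rule beside the outcome.

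**Step 1. Meaning of the outcome.** One sentence assigns it to WP1B, WP2 and WP3 together. In WP1B, where patients enter at WHO class 5-6, it can only sensibly mean progression to IMV. WP1A uses need in the same sense. Ventilation duration and ventilator-free days are listed separately as secondary outcomes, which suggests that the primary outcome is not a measure of duration or liberation.

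**Step 2. Apply that meaning to each work package.**

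| Work package | IMV required for entry? | Can any IMV vary? |
|---|---|---|
| WP1B | No (WHO class 5-6) | Yes |
| WP2 | Yes, during ICU stay | No |
| WP3 | Yes, during ICU stay | Only if counted after the 10-day course, or as continued ventilation |
| WP4 | Yes, during ICU stay | No, insofar as the outcome is carried over |

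For WP2, P(IMV | included) = 1 in both exposure groups. Risk difference = 1 − 1 = 0; risk ratio = 1/1 = 1; the odds ratio is not estimable. I write about 100% because a first intubation after day 28, or extracorporeal support without IMV, would be marginal exceptions.

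**Step 3. Selection, by illustration.** The rates below are assumptions, not figures from the document. Take ICU patients whose corticosteroids start before intubation. Control risk of IMV is 60%; 28-day mortality is 30% if intubated and 5% if not; treatment changes mortality only through the risk of intubation.

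- Control mortality: 0.60 × 0.30 + 0.40 × 0.05 = 20.0%.
- IMV risk × 0.7 (42%): 0.42 × 0.30 + 0.58 × 0.05 = 15.5%.
- IMV risk × 0.8 (48%): 0.48 × 0.30 + 0.52 × 0.05 = 17.0%.
- IMV risk × 0.9 (54%): 0.54 × 0.30 + 0.46 × 0.05 = 18.5%.

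Among intubated patients only, the comparison is 30% with 30% for mortality and 100% with 100% for IMV. In this set-up, a true mortality reduction of 1.5 to 4.5 percentage points disappears from both primary outcomes. This shows the mechanism, not its size in this study. For patients already intubated when corticosteroids start, the IMV criterion selects nothing.

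**The case against.** The strongest reply is that the outcome is undefined rather than void, and that a condensed article may leave exact endpoint definitions to the full protocol or analysis plan. In a ventilated cohort it could mean still needing IMV at day 28, which does vary. That reading is possible, but no sentence in the article supports it, and the same words serve WP1B. It would also need a rule for deaths: someone who dies before day 28 is not ventilated on day 28. Having 28-day survival as a second primary outcome makes those deaths visible but does not repair the ventilation outcome.

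It is also fair to say that ventilated ICU patients are a legitimate target population, that the main logistic model names only survival at day 28, and that ventilation is still measured through secondary outcomes. All of that stands. It limits the damage but does not make the stated primary outcome informative in WP2.

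A reader might infer more than the document supports:

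- **That every patient has the event on entry.** The rule is IMV at some time in the ICU stay, so the event is guaranteed by eligibility but need not be present on the first day.
- **That WP3 has no power on this outcome.** Its question begins after 10 days of dexamethasone. A patient ventilated earlier may by then be extubated, so counting from that point could give a varying outcome.
- **That WP4 fails as a whole.** The IMV outcome reaches it only through the cross-reference. The Statistical Analysis section has WP4a test effect modification on mortality, and WP4b compares transcript levels between treated and untreated patients.
- **That 28-day survival is shown to be biased.** This requires corticosteroids started before intubation and an effect on intubation. The document gives neither.

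**Conclusion.** The concern holds for WP2: on the reading that the article's own wording favours, one of two primary outcomes is fixed at about 100% in both groups and cannot show an effect. In WP3 the outcome lacks the definition that would make it informative. In WP4 the problem exists only as far as the outcome is carried over.

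The risk to 28-day survival in WP2 is real but conditional. It applies to patients whose corticosteroids start before intubation. Their share is not given, so the bias cannot be sized. The conclusion rests on reading need for IMV as any IMV and on no time zero being stated for the 28 days.

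**What to change.** **Outcome.** In WP2 and WP3, and in WP4 where it is used, replace 28-day need for IMV with a ventilation outcome that can vary in ventilated patients and handles death. Ventilator-free days to day 28 with death scored 0 would promote an existing secondary outcome. Time to liberation from IMV with death as a competing event is the alternative. WP1B can keep the present outcome.

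**Time zero.** State it, and assess eligibility with information known then.

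- WP2: the start of IMV.
- WP3: the end of the 10-day course, in patients ventilated at that point.

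The 48-hour rule in WP2 should not simply be dropped. The Interventions section defines exposure as at least 3 consecutive days, so without a landmark, early deaths and discharges could fall into the unexposed group by default. Apply any minimum-stay or minimum-exposure rule as the same landmark in both groups.

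**Cost.** Mostly wording. The WP2 question narrows to ventilated patients. Ventilation start and stop dates must be available; Data Collection specifies daily recording only for corticosteroids, so this needs checking. Widening WP2 to all ICU admissions would let need for IMV remain an outcome, but the article does not show that the collaborating ICU datasets hold never-ventilated patients.
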